### Compensation

Participants will receive $400 for taking part in this study – $125 at enrollment and exit, and $50 at the 3-, 6-, and 9-month viral load assessments. Compensation will be offered using ClinCard. ClinCard is a MasterCard-branded debit card that can be loaded with funds by the study team. The card will be loaded according to the payment schedule (enrollment, 3-, 6-, 9-, and 12-months).

This card is administered by a company called Greenphire. Greenphire requires name, address and date of birth entered online for payment; mobile phone number and/or email address are optional and only for study related communications. This information will only be used for payment and communication purposes and will not be given to another company or linked to any of the study data. Greenphire will not receive any information about client health status or the study in which they are participating.

If the card is lost or stolen, participants are instructed to call the study team for a replacement card. Participants are further instructed that losing the card is similar to losing cash; any money previously loaded on the card cannot be recovered.

Some participants may be eligible for cash payments. These cases are rare and may be offered based on the study team’s judgement.

## Measures to Minimize Bias: Randomization

Randomization is a process that assigns participants/subjects by chance (rather than by choice) into specific groups, typically for clinical research and clinical trials.

The goals of randomization include:

- - - 1. To produce groups that are comparable (balanced)
      2. To remove bias (selection bias)
      3. To guarantee the validity of statistical tests

INSTACARE follows a stratified block randomization structure. Block randomization is designed to ensure a balance in sample size across groups over time. Blocks are small and balanced with predetermined group assignments, which keeps the numbers of subjects in each group similar at all times. Block size should be a multiple of the number of groups. INSTACARE has two study arms, or groups: the CHW (intervention) group and the Usual Care (control) group. The groups are stratified by sex (male, female) with a block size of 6. Subject allocation is implemented using the randomization module in REDCap, which also monitors the overall allocation progress and assignment of randomized subjects. As a minimal risk study, the investigative team does not anticipate the need to unblind the trial due to patient safety concerns or serious adverse events. As a precaution, the project statistician can be unblinded to the randomization through REDCap. The PI can use REDCap’s Randomization Dashboard to view the overall allocation progress and assignments for subjects that have been randomized. Subjects are randomized by a research coordinator blinded to the sample.

## Study Intervention Compliance

Participants have up to 6-weeks after their scheduled follow-up date to complete labs. After 6-weeks, the entry will be marked as MISSED. Participants will not be compensated for missed F/U appointments.

Participants in the control group will receive a call at least two weeks before their quarterly follow-up to remind them to complete their labwork and/or survey. Clients can complete labs up to six weeks past their follow-up due date. For the 3- and 9-Month follow-up appointments, CHWs can attempt to contact participants weekly for up to 6-weeks after the due date. At the 6- and 12-Month F/U appointments, CHWs will attempt to reach all participants by phone to schedule and complete their survey which can be in person or by phone. Attempts to contact participants by phone should occur at different times and days of the week including evenings and weekends. Those that cannot be reached should also have a letter delivered to their address on file (when feasible) asking them to call the study team.

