**Enrollment Procedures**

*Note: All enrollment procedures should be conducted in person.*

- **Data Entry Procedure**

1. Log into REDCap, select “My Projects” from the header, and select ”[INSTACARE: Integrated Navigation Services for Treatment Adherence, Counseling, and Research](https://redcap.miami.edu/redcap_v14.0.12/index.php?pid=7479)”
2. Select Add/Edit Records from the menu on the lefthand side of the page
3. Enter the new Client ID and press enter
4. Complete all documents listed under ***Baseline Enrollment***:
   1. **Informed Consent**
      1. **For Spanish- or Kreyol-speaking clients**: a member of the research team is available to translate the consent form for the client’s comfort. Note: Patients must speak/understand basic English to be eligible for enrollment.
      2. **Client unable to provide digital signature on REDCap**: If a participant is unable to digitally sign the informed consent form during the enrollment process, they must sign a paper copy of the ***Informed Consent Form*** for our records. The CHW should sign the electronic record and enter the following field note: “Client signature captured on file.”
   2. Intake Information
   3. INSTACARE Health Survey

- For each form, ensure all questions are completed. If so, at the end of the page, you will select “Complete” at the question called “Form Status”. The click “Save & exit form.”
- Once the INSTACARE Health Survey is complete, the CHW must contact the research coordinator for randomization. RC will indicate if the participant was assigned to the intervention or the control group (usual care).
- Clients randomized to the intervention will be assigned based on demographics (e.g. Kreyol speaking, etc.) and current CHW workload. Half of all participants will be assigned to the Usual Care group.

1. Provide payment ($125 for baseline) to participant via [ClinCard](https://miamiedu.sharepoint.com/:b:/r/sites/CHAMPSTRONG/Shared%20Documents/General/INSTACARE/ClinCard/ClinCard%20Reference%20Guide%20-%20UM%20Site%20Coordinator%205.21.pdf?csf=1&web=1&e=akAvmv) System
   1. Complete W-9; have client sign paper receipt
   2. Participants randomized to the CHW group will be assigned to a CHW within one month of initial *referral* and within one week of enrollment.

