### CHW Intervention

Interactions between CHWs and patients will occur through a) clinic visits, b) home visits, and c) phone or mobile contact.

*Note: Refer to the INSTACARE (COACH) Workbook for CHW guide

- **Baseline “Getting to Know You”**: The baseline patient evaluation is estimated to take 90 minutes.

Within one week of being assigned a patient, CHWs will schedule a meeting to perform a comprehensive, face-to-face evaluation of the participants' socioeconomic, social support, and healthcare barriers to ART adherence, including:

- Stability of housing, food, immediate resources, social support, immigration status, life stressors
- Barriers to interacting with the healthcare system such as communicating with providers, transportation needs, insurance status, and unmet mental health needs
- Understanding HIV and HIV medications
- Knowledge of their own VL (patient ability to self-monitor VL changes) Current lifestyle behaviors, including use of cigarettes, alcohol and/or non-prescribed drugs, and transmission risk behaviors (e.g. condom use, disclosing HIV status to partners, multiple sexual partners)
- Communication preferences, (e.g. mobile phone knowledge and usage)

*Note: While INSTACARE is focused on improved VL through increased ART adherence, CHWs also address these issues from an overall health and general well-being approach.

- **Individual Action Plan**: After the evaluation, review each participant's unique circumstances and work with the client to design an individualized plan to overcome barriers to ART adherence, beginning with the most pressing needs.
- **Months 1-3**
  1. Conduct an average of one face-to-face weekly visit to provide acute support focused on HIV management and HIV education for the first month of enrollment. Face-to-face meetings can gradually be replaced with phone calls beginning in Month-2 depending on the severity of your clients’ needs
  2. Accompany participants to the majority of their medical appointments and review treatment plans to ensure they understand provider recommendations.
  3. Based on individual needs and preferences, engage participants in problem-solving processes to set priorities for immediate problem resolution
  4. Set personal health goals regarding VL control (i.e., improved ART adherence, addressing barriers to care, resolving ambivalence about HIV treatment)
  5. Develop a plan to accomplish those goals and review results

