# STUDY ASSESSMENTS

## Study Assessments

Medical data, including HIV viral load, from the 300 participants will be obtained from the electronic medical records. The study team will maintain a separate, secure database at UM having information on participant age, race, ethnicity, ZIP code, and group assignment. Additional data on several areas related to HIV management, including medication adherence and self-efficacy will also be collected. Data will periodically be transferred from UM’s secure database to REDCap, UM’s web-based clinical research management application for clinical and translational research. Below lists the assessments that will be used for patient tracking, as well as the CHW training evaluation.

| **Specific Aim 1: Primary Measures** | | Durable HIV viral suppression prevents forward transmission of HIV, making HIV treatment synonymous with HIV prevention. The primary outcome is binary: HIV viral suppression (plasma HIV VL of < 200 copies/mL) at the 12-month follow-up. As part of usual medical care, patients have VL checked every 3 months. Thus, data on the primary outcome will be abstracted from the electronic medical record by a study coordinator. All patients who are not up to date on VL measurements will be encouraged to go to their assigned laboratory (JHS, Quest or LabCorp) to have the test done. By Month-11 of enrollment, the staff will call participants to ensure Exit is scheduled on time. |
| --- | --- | --- |
| Viral Load Suppression | Plasma HIV RNA  (>200 copies / mL) |  |
| **Specific Aim 1: Secondary Measures** | |  |
| ART Adherence | Medication adherence (ACTG Adherence Questionnaire) |  |
| Non-HIV Medical Care | Medical Records |  |
| Hospitalizations | Medical Records |  |

| **Specific Aim 2: Primary Measures** | |
| --- | --- |
| ***Structural*** | |
| Social Determinants of Health | Health-Related Social Needs (HRSN) |
| Racism | Index of Race-Related Stress-Brief (IRRS-B) |
| Food Security | Household Food Insecurity Access Scale (HFIAS) |
| ***Institutional*** | |
| Dr-Pt Interaction | Doctor-patient communication questionnaire: empathy, decision-making, listening |
| HIV Stigma – Clinic Setting | Perceived Discrimination Scale: Discrimination, mistreatment, quality of care, & mistrust from healthcare system |
| ***Community*** | |
| HIV Stigma – Community Setting | HIV Stigma Scale – Short Version: Perceptions of stigma, disclosure concerns, concerns with public attitudes and negative self-image |

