**Secondary Efficacy Endpoint(s):**

SPECIFIC AIM 2: Examine the effect of a clinic-based CHW-led MI intervention vs UC on Socioeconomic & Psychosocial Determinants of Health. Social Determinants of Health (SDOH) are drivers of health disparities and evidence demonstrates improved SDOH leads to improved health outcomes. INSTACARE’s CHW intervention aims to address the negative SDOH impacting HIV health among participants. These determinants are assessed using the validate measures included in the INSTACARE Health Survey delivered at baseline, 6-months, and study exit.

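### Intervention CHWs may also collect the 6- and 12-month surveys, so the self-reported Aim 2 scales are open to reporting bias that differs by arm

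*Protocol*

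**What the plan says.** Under Study Intervention Compliance, the protocol says of the 6- and 12-month follow-ups: "CHWs will attempt to reach all participants by phone to schedule and complete their survey which can be in person or by phone". This covers both arms.

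The same staff role delivers the intervention. The CHW Intervention section says: "Interactions between CHWs and patients will occur through a) clinic visits, b) home visits, and c) phone or mobile contact". The month-by-month outline there has CHWs coaching adherence, setting viral-load goals, and building self-efficacy and social support.

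The survey is the source for Aim 2. Under Secondary Efficacy Endpoint(s): "These determinants are assessed using the validate measures included in the INSTACARE Health Survey delivered at baseline, 6-months, and study exit". The Study Assessments tables list ten Aim 2 primary measures: social needs, race-related stress, food security, doctor-patient communication, stigma in the clinic, stigma in the community, social support, MOS-HIV quality of life, adherence self-efficacy and empowerment. All are topics on which the participant reports. Adherence, an Aim 1 secondary measure, is listed as "Medication adherence (ACTG Adherence Questionnaire".

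Three further statements limit the scope:
- At baseline, "Once the INSTACARE Health Survey is complete, the CHW must contact the research coordinator for randomization". The first survey therefore precedes allocation.
- For viral load, "data on the primary outcome will be abstracted from the electronic medical record by a study coordinator".
- The one blinding statement about a staff role in current conduct is "Subjects are randomized by a research coordinator blinded to the sample".

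**The concern.** The constructs that the CHW works on with a participant for up to 12 months are the constructs that the survey scores. If the same CHW, or a close colleague, then asks the questions, intervention participants may answer to please a coach or may disclose more to someone they trust. Usual-care participants have no coaching relationship to protect. Differences between arms on these scales would then mix a real effect with a reporting effect, and the analysis cannot separate the two.

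Aim 2 is the secondary efficacy objective, and the mediation models take their mediators from the secondary outcomes. A reporting difference by arm enters path a (intervention to mediator) directly. It would also distort the product a*b wherever path b is not zero.

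**Working it through.** **Reading the provisions together.** The protocol states no figure on this point, so there is none to reproduce. The check is whether anything breaks the link between delivering the intervention and collecting the outcome.

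1. Collector at 6 and 12 months: CHWs, for all participants, in person or by phone.
2. Deliverer of the intervention: CHWs.
3. Rule keeping the assigned CHW from collecting: none.
4. Self-completion as the stated mode: none. A survey completed in a phone call with a CHW cannot be read as self-administered.
5. Masked or independent interviewer: none. The section on measures to minimize bias deals only with randomization.
6. Timing: baseline is collected before allocation, so the asymmetry arises only afterwards. Adjusting for baseline scores cannot remove it.

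**Illustration of size.** The bias sizes are assumptions, because the protocol gives none. The other inputs come from the Sample Size Determination section: 150 per arm, two-sided alpha 0.05, and 20% attrition, which leaves 150 × 0.8 = 120 per arm. The Bonferroni correction comes from the section on analysis of the secondary endpoints. Its divisor is not stated there, so I assume 10, one for each Aim 2 primary scale.

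For a two-sided z-test of two means with true effect 0 and a reporting shift of b SD in one arm:

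P(reject) = 1 − Φ(z_c − b/SE) + Φ(−z_c − b/SE), with SE = √(2/n)

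At n = 150, SE = √(2/150) = 0.1155, so b/SE = 0.866, 1.732 and 2.598 for b = 0.1, 0.2 and 0.3. The critical values are z_c = 1.960 at alpha 0.05 and z_c = 2.807 at alpha 0.05/10 = 0.005.

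| Setting | b = 0.1 | b = 0.2 | b = 0.3 | Nominal |
|---|---|---|---|---|
| 150 per arm, alpha 0.05 | 13.9% | 41.0% | 73.8% | 5% |
| 150 per arm, Bonferroni over 10 | 2.6% | 14.1% | 41.7% | 0.5% |
| 120 per arm, alpha 0.05 | 12.1% | 34.1% | 64.2% | 5% |
| 120 per arm, Bonferroni over 10 | 2.1% | 10.4% | 31.5% | 0.5% |

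Counting adherence as an eleventh outcome changes little: about 2%, 13% and 41% at 150 per arm, against a nominal 0.45%. The error rate is higher at 150 than at 120 per arm because a larger sample detects a fixed bias more reliably. Bonferroni lowers the rates but leaves the bias in the estimates.

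**The case against.** The strongest reply is that this is a staffing choice in a pragmatic trial, that it touches only secondary self-report scales, and that several tempting extensions go beyond the text. Much of that stands.

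- A reader might infer that the trial's main result is at risk. It is not. Viral load is a laboratory value taken from the medical record, and hospitalizations and non-HIV care also come from records.
- A reader might infer that every Aim 2 outcome is affected. The two Aim 2 secondary measures are not participant surveys: MITI 4 is scored by a motivational interviewing expert, and delivery strategies come from CHW logs.
- Including adherence is an inference. The protocol does not say who administers the ACTG questionnaire or that it is part of the Health Survey, although it names no other collector.
- A reader might infer that the coach is always the interviewer and that usual-care participants face a stranger. The text permits the first but does not require it. CHWs also explain consent and run baseline enrolment for everyone, and may contact participants around the 3- and 9-month dates. A bias confined to the CHW arm is therefore a worst case.
- A reader might infer that all scales shift in favour of the intervention. Greater trust could instead raise reported stigma, race-related stress or unmet needs, which would count against the CHW arm.
- The Sample Size Determination section mentions a standardized difference of 0.10 for secondary outcomes. That is a power statement and not a threshold for interpretation, so its match with the smallest assumed bias proves nothing.

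What does not stand is the suggestion that the wording leaves the matter open. Saying that participants complete their 6-month assessment does not settle who asks the questions, and the compliance section gives CHWs the task.

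**Conclusion.** The point holds for the ten Aim 2 primary scales, for the mediation a-paths built on them and, by inference, for ACTG adherence. As written, the protocol allows the person who delivered the intervention to collect the self-reports used to judge it, and provides no safeguard. The likely direction favours the CHW arm for adherence, self-efficacy, social support and empowerment. For stigma, race-related stress and social needs it is uncertain.

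The size is unknown. The rejection rates in the table depend on assumed shifts of 0.1 to 0.3 SD in one arm only, no true effect, and a simple comparison at one time point. They show what a bias of that size would do, and are no evidence that one of that size will occur. Because the primary endpoint is untouched and the remedy is inexpensive, this is a worthwhile improvement and not a fault that threatens the trial's main conclusion.

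**What to change.** Amend the Study Intervention Compliance section so that:

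- the assigned CHW may help to schedule the 6- and 12-month surveys but does not administer them;
- they are administered by a CHW never assigned to that participant or by the research coordinator, or are self-completed on the study tablet where feasible;
- the procedure is the same in both arms;
- mode and interviewer are recorded for each survey, to support a sensitivity analysis.

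State also who administers the ACTG adherence questionnaire, and bring it under the same rule.

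No new role is needed. CHWs already survey usual-care participants, assignment by demographics and workload implies several CHWs, and the survey is already a REDCap form. The cost is protocol wording, some rescheduling among existing staff, whose numbers the protocol does not give, and possibly slightly lower completion. Self-completion should stay optional, since the protocol describes a population with severe poverty and homelessness and provides for Spanish and Kreyol speakers.

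The change does not remove all bias. Participants know their arm, and the coordinator who relays allocations is not masked to them. State this as a limitation for the self-reported outcomes.

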# SUBJECT DISCONTINUATION/WITHDRAWAL

## Subject Discontinuation/Withdrawal from the Study

Participants are free to withdraw from participation in the study at any time upon request. However, we seek to minimize participant withdrawal from the study by ongoing engagement as described above for the intervention group.

Clients seeking to withdraw from the study can be asked to complete the exit assessment and can receive $50 compensation for completing the assessment at time of withdrawal.

Clients who sign the informed consent form and are randomized but do not receive the study intervention may be replaced. Participants who sign the informed consent form, and are randomized and receive the study intervention, and subsequently withdraw, or are withdrawn or discontinued from the study, will not be replaced.

## Lost to Follow-Up

A participant will be considered lost to follow-up if he or she is unable to be contacted by the study site staff for 3-months. Before a participant is deemed lost to follow-up, the staff will make every effort to regain contact with the participant (where possible, weekly phone calls, calling/visiting emergency contacts, performing house visits, and if necessary, a delivering a letter to the subject’s last known mailing address or local equivalent methods). These contact attempts should be documented in the client’s study file.

After 3-months, the client will be considered **Lost to Follow-Up**. Additional contact attempts made by the CHWs will be limited to one quarterly phone call/voicemail reminding clients of upcoming lab/assessment dates. Lost to Follow-Up clients will not be withdrawn from the study, as findings from our pilot intervention suggest clients may return seeking support at a later date. Participants that resurface within the 12-month intervention period can continue to receive support until their scheduled exit date.

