## Risk/Benefit Assessment

### Known Potential Risks

Potential risks include emotional distress and breach of privacy/confidentiality. It is possible someone not involved in this study could access patient information, or patient confidentiality may be breached from their participation in this study. As a clinic and community-based intervention, it is possible that someone from the community may observe a participant receiving care. To minimize risks these risks, CHWs are instructed to dress in a manner that is culturally consistent with norms within each participant’s neighborhood. Specifically, CHWs do not wear scrubs or any type of clothing that indicates they work in the healthcare field. Further, CHWs do not wear their clinic id badges in the field, as this could be used to associate them with a healthcare system. It is also possible that a participant could become emotionally distressed during counseling. If this occurs, the study team will refer the participant to mental health services at the healing place, a Jackson Health System mental health clinic focused specifically on PLH. It is possible that privacy regarding study participation could be breached if a participant’s phone is lost stolen or taken without their explicit consent. To minimize these risks, study team members will not leave any specific study-related information in voicemails or text messages; they will also confirm they are speaking with the participant prior to any appointment scheduling over the phone. Building social support is one-way CHWs will help participants. However, before a CHWs meets anyone in a participant’s social network, they will discuss whether the participant is comfortable explaining the CHWs role to their support system. Among participants who not comfortable disclosing their relationship with their CHW, CHWs will discuss alternative approaches to integrating social support without disclosing the participant’s study participation.

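### The voicemail reminder for participants lost to follow-up contradicts the protocol's own rule on what a voicemail may contain

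*Protocol*

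**What the plan says.** Two sections of the protocol govern what may be left on a participant's phone.

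- **Known Potential Risks** (under Risk/Benefit Assessment) recognises that "privacy regarding study participation could be breached if a participant’s phone is lost stolen or taken without their explicit consent". Its safeguard is that "study team members will not leave any specific study-related information in voicemails or text messages". It adds, for live calls, that "they will also confirm they are speaking with the participant prior to any appointment scheduling over the phone".
- **Lost to Follow-Up** (under Subject Discontinuation/Withdrawal) applies once a participant has been out of contact for 3 months. From then on, CHW contact is reduced to "one quarterly phone call/voicemail reminding clients of upcoming lab/assessment dates". The section does not refer back to the voicemail safeguard and offers no neutral wording.

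A third section is a useful comparison. Under Study Intervention Compliance, participants who cannot be reached by phone for their survey may be sent a letter, and the only content described for it is a request to call the study team.

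**The concern.** The voicemail safeguard covers all study team members and all voicemails and texts, and it makes no exception for participants who are hard to reach. The later section then specifies a voicemail whose stated purpose is to convey lab and assessment dates. A CHW cannot leave that message and also keep the promise made in the risk section.

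The conflict matters because of whom it affects. The safeguard exists for the case where the phone is out of the participant's control. Someone who has not answered for 3 months is more plausibly in that position than someone in regular contact. Under Incarcerated Participants, a person jailed after enrolment is classed as lost to follow-up automatically, and the reminder rule makes no exception for that group. Breach of privacy or confidentiality is one of the two risks with which the risk section opens, so this safeguard is not incidental. If the text stays as it is, some staff will follow one section and some the other.

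**Working it through.** No arithmetic applies. The point depends on no rate, sample size, effect or error level, so the check is a comparison of the texts.

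1. **Who is bound.** The safeguard binds study team members. The reminder is assigned to CHWs, who are study team members. The same people fall under both rules.

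2. **Which channel.** The safeguard names voicemails and text messages. The reminder rule names a phone call or a voicemail. They overlap on voicemail.

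3. **What content.** The safeguard excludes any specific study-related information. The full reminder rule reads "Additional contact attempts made by the CHWs will be limited to one quarterly phone call/voicemail reminding clients of upcoming lab/assessment dates". The reminding clause follows both the call and the voicemail and is not confined to the call. On the plain wording, the dates are the content of the voicemail.

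4. **Is that content study-related?** An assessment date is, since the assessments exist only because of the study. A lab date is less clear, because Study Assessments describes viral load testing every 3 months as part of usual care. However, the Compensation section pays participants for the 3-, 6- and 9-month viral load assessments, so the quarterly lab dates also serve as study follow-up dates. Even if lab dates are set aside, the assessment dates leave the conflict standing.

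5. **Does another rule resolve it?** The identity check covers appointment scheduling by phone. It does not mention reminders, and it cannot be carried out on a voicemail. The only phone script that the protocol names is for recruitment calls (Strategies for Recruitment and Retention). Nothing in Lost to Follow-Up limits the message.

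6. **Can both aims be met?** Yes. The letter under Study Intervention Compliance, which asks only for a call back, already meets the standard of the risk section. The conflict comes from wording and is not forced by the follow-up schedule.

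Result: the two sections contradict each other on the content of a voicemail. Live calls are not affected.

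**The case against.** The strongest reply is that the sections can be read together. The risk section sets a study-wide rule on message content, while Lost to Follow-Up sets how often contact is made and why. A careful CHW could leave a neutral message and give the dates when the participant calls back. That is sensible practice and probably what was intended. It is not what the text says, because the reminder content attaches to the voicemail as well as the call. The reply does show that a short clarification is enough.

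Three stronger readings are tempting, and the document does not support them.

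- **That tracing through emergency contacts is forbidden.** Lost to Follow-Up lists "calling/visiting emergency contacts, performing house visits" among the steps for regaining contact. A reader might set this against the statement that, before a CHW meets anyone in the participant's social network, "they will discuss whether the participant is comfortable explaining the CHWs role to their support system". That statement is a condition and not a ban. It belongs to the account of building social support, and the discussion could have taken place while the participant was still in touch. Tracing is also assigned to staff in general ("the staff will make every effort to regain contact with the participant") and takes place before the participant is classed as lost. The intake form is not reproduced and the consent pages are not available here, so it cannot be said that participant-approved contacts are missing.
- **That HIV status is disclosed.** The reminder concerns dates, and nothing says that HIV is mentioned. The phone risk that the protocol names is exposure of study participation.
- **That the number of offending voicemails can be estimated.** Sample Size Determination mentions 20% attrition, and 0.20 × 300 = 60 participants. That figure is a power scenario and not a forecast of loss to follow-up. The number of reminders per person depends on when contact was lost, and each contact may be a live call.

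**Conclusion.** The contradiction holds for voicemail content. Lost to Follow-Up prescribes a message that Known Potential Risks rules out, for participants not reached for 3 months. What is at stake is disclosure of study participation, which the protocol itself identifies as a risk.

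The size is minor to moderate, as a matter of participant protection. Sample size, power and the primary analysis are not shown to be affected. The conclusion rests on two readings: that the reminding clause applies to the voicemail as well as the call, which is the plain sense of the sentence, and that a study assessment date counts as specific study-related information. It does not depend on how many participants are lost.

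**What to change.** Reconcile Lost to Follow-Up with Known Potential Risks in a sentence or two:

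- Any voicemail is a neutral request to call back and does not mention labs, assessments or the study.
- Lab and assessment dates are given only in a live call, after the caller has confirmed that the participant is on the line.

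This brings voicemails into line with the call-back letter already described under Study Intervention Compliance. As an optional addition, Lost to Follow-Up could cross-refer to the disclosure safeguard in Known Potential Risks where emergency contacts are approached, so that staff know what governs what they may say.

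The change costs a few words in one section. The one drawback is that a neutral message may bring in slightly fewer participants for labs than an explicit reminder would.
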